### Sample size

We have performed sample size calculations for chronic dizziness according to other studies on the same disease using the same primary outcome measure because no such acupuncture research has been reported [19-21]. The estimated sample size was calculated considering previous DHI results. Calculations are performed using 80% power and a (two-sided) 5% significance level. Estimations indicated 263 individuals for the DHI assessments (effect size = 0.41; standard deviation = 0.7), where effect size is the mean difference expected between the two groups and standard deviation is for the population. We plan to enroll a total of 100 participants with 50 in each group, allowing for a 15% withdrawal rate.

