**Methods/Design:**

This trial is a randomized, single-blind, controlled study. A total of 80 participants will be randomly assigned to two treatment groups receiving acupuncture and sham acupuncture treatment, respectively, for 4 weeks. The primary outcome measures are the Dizziness Handicap Inventory (DHI) and the Vertigo Symptom Scale (VSS). Treatment will be conducted over a period of 4 weeks, at a frequency of two sessions per week. The assessment is at baseline (before treatment initiation), 4 weeks after the first acupuncture session, and 8 weeks after the first acupuncture session.

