### Population

Patients will be recruited in the acupuncture clinic at Beijing Hospital of Traditional Chinese Medicine, affiliated to Capital Medical University, with a target sample size of 100 subjects. Our trial will be promoted by a poster at this hospital. All candidates will go through a standardized interview process and receive more information about the study and the treatments. Patients will be informed in a manner suggesting that two different types of acupuncture treatment will be compared. One type will be traditional acupuncture and the other will be a new type of acupuncture, and the efficacy of both types is uncertain. Terms such as ‘placebo’ or ‘sham’ will not be mentioned. The participants’ written consents will be obtained. The purpose and procedures, and potential risks and benefits of the study will also be explained thoroughly to the participants. Participants will be able to withdraw from the study at any time without consequence. The trial will be executed from February 2013 to December 2015. All recruit procedures will be recorded in a log file (Figure 1).

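### The stated sample-size inputs require 92 to 94 evaluable participants, not 263, and 263 is not reconciled with the 100 to be enrolled or the 80 in the abstract

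*Protocol article*

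**What the plan says.** The Sample size section bases the calculation on earlier DHI results. It gives the error rates: "Calculations are performed using 80% power and a (two-sided) 5% significance level". It then gives the result with its inputs: "Estimations indicated 263 individuals for the DHI assessments (effect size = 0.41; standard deviation = 0.7". It says what the inputs mean: "where effect size is the mean difference expected between the two groups and standard deviation is for the population". The next sentence sets the enrolment: "We plan to enroll a total of 100 participants with 50 in each group, allowing for a 15% withdrawal rate".

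The Population section agrees on enrolment ("with a target sample size of 100 subjects"), but the Methods/Design part of the abstract does not: "A total of 80 participants will be randomly assigned to two treatment groups".

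The DHI section describes 25 items scored 0, 2 or 4, with severity bands that run up to 100. The Data analysis section names repeated-measures analysis of variance for the group comparison and gives no correlation between visits.

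**The concern.** One short section gives a required size of 263 and a planned size of 100, with nothing to connect them. The inputs printed beside 263 do not produce it either. This section is the only justification of the trial's size, and it rests on one of the two primary outcomes.

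If the section stands, a null result will be read as coming from a trial with 80% power. Readers cannot tell whether the trial is about ten participants short or has roughly a third of the participants it needs. The abstract's 80 adds a third candidate for the planned size.

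**Working it through.** **Inputs** (Sample size section): mean difference 0.41; SD 0.7; power 80%; two-sided alpha 5%; 1:1 allocation (50 per group); 15% withdrawal. The standardised difference is d = 0.41 / 0.7 = 0.586.

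**Step 1. Try to reproduce 263.**

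n per group = 2 × (1.960 + 0.842)² × (0.7 / 0.41)² = 45.8, rounded up to 46.

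The t-test solution is 46.7, rounded up to 47. The total is therefore 92 to 94 evaluable, and 263 is not reproduced. With 263 in total, power at d = 0.586 would be 99.7%.

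Other readings at the stated alpha and power also fail:

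| Reading | Evaluable total | Total with 15% withdrawal |
|---|---|---|
| 0.41 as raw difference, SD 0.7 (as defined) | 92 | 109 |
| 0.41 as a standardised effect | 188 (190 by t test) | 222 (from 188) |
| 0.41 × 0.7 = 0.287 as a standardised effect | 382 (191 per group) | 450 |

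**Step 2. What would 263 imply?** For 263 in total to give 80% power, d must be about 0.347. That is a difference of 0.347 × 0.7 = 0.24 at SD 0.7. If 263 were the evaluable number, enrolment would have to be 263 / 0.85 = 309.4, so 310.

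**Step 3. Does 100 meet the requirement from the stated inputs?** 92 / 0.85 = 108.2 and 94 / 0.85 = 110.6. Rounded up to whole participants and equal groups, that is about 109 to 112 enrolled. The plan enrols 100, and 100 × 0.85 = 85.

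**Step 4. Power of a two-sample t test (noncentral t, two-sided 5%).**

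| Scenario | Evaluable | Power |
|---|---|---|
| d = 0.586, 100 enrolled, no loss | 50 / 50 | 82.6% |
| d = 0.586, 100 enrolled, 15% loss | 43 / 42 | 76.1% |
| d = 0.586, 80 enrolled, 15% loss | 34 / 34 | 66.3% |
| 0.41 is a standardised effect, 100 enrolled, 15% loss | 43 / 42 | 46.3% |
| 263 in total is the true requirement (d = 0.347), 100 enrolled, 15% loss | 43 / 42 | 35.2% |

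With 43 / 42, 80% power is reached at d = 0.615, a difference of 0.615 × 0.7 = 0.43.

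**Step 5. Scale of the inputs.** The DHI total runs from 0 to 100 (25 items × 4), and the severity bands are about 30 points wide. A difference of 0.41 with an SD of 0.7 is hard to place on that scale, and the section names no other.

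**The case against.** **The planned analysis is not a two-sample test.** The protocol names repeated-measures analysis of variance. Suppose the group test averages the 4-week and 8-week values with equal variances. The variance then falls by a factor (1 + r) / 2, where r is the correlation between the two visits. With 85 evaluable, power is 80.3% at an assumed r of 0.8 and 84.7% at 0.6. A reader might infer from the table above that the trial cannot reach 80% on any reading. The documents do not support that: for the planned analysis at 0.41 and 0.7, the 80% is unsupported rather than refuted. What remains is that no correlation is stated and the calculation takes no credit for one.

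**Some settings do give 263.** It would be tempting to say that none does. A standardised effect of 0.41, two-sided alpha 0.025 and 80% power give 228 in total, and 228 × 1.15 = 262.2, rounded up to 263. So 263 may be a genuine result of other inputs. This route contradicts both the stated 5% level and the stated definition of effect size, so it does not rescue the section.

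**On the stated inputs the shortfall is small.** This is true: about four points of power, or about ten participants, and none if nobody withdraws. But the section itself allows for 15% withdrawal, and the small shortfall assumes that 263 is the mistaken figure.

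**Conclusion.** The section is wrong as written. Its inputs give 92 to 94 evaluable, not 263, and 263 is not reconciled with 100 or with the abstract's 80. This is arithmetic on figures that the protocol itself states and defines.

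The effect on power depends on which figure is right. For a two-sample comparison with 85 evaluable, it is about 76% if 0.41 and 0.7 are right as defined, about 46% if 0.41 is a standardised effect, and about 35% if 263 in total is the true requirement. At 80 enrolled and the inputs as defined, it is about 66%.

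A reader might conclude that 263 is a slip and that no more participants are needed, or that the trial has only a third of the participants it needs. The documents support neither. The inputs are attributed to earlier studies that are not shown, and the unexplained scale of 0.41 and 0.7 is itself a reason not to assume that they are the correct figures.

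**What to change.** 1. Establish the source, scale and units of 0.41, 0.7 and 263, and say how they relate to a DHI scored 0 to 100.
2. Correct or delete 263.
3. Use one enrolment figure in the abstract, the Population section and the Sample size section.
4. Restate the power that this figure delivers after 15% withdrawal:
   - If 0.41 and 0.7 are confirmed as defined, state 46 to 47 evaluable per group. For 100 enrolled, state about 76% power, or 80% power for a difference of 0.43. Alternatively, state the between-visit correlation under which the planned analysis reaches 80%, with its source.
   - If 263 in total is confirmed, disclose that 85 evaluable gives about 35% power.
   - If 0.41 proves to be a standardised effect, disclose about 46%.

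The restatement means rewriting one section and correcting one number in the abstract. The trial is still recruiting, so this can be done before analysis. The downside is that the stated power becomes less favourable. Whether more is needed than a restatement cannot be judged until step 1 is done.

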### Primary outcome measures

#### Dizziness Handicap Inventory

The Dizziness Handicap Inventory (DHI) is a validated, self-reported questionnaire, which is widely used to evaluate the functional, emotional, and physical impact of dizziness on patients’ daily life. It consists of 25 questions about daily problems associated with dizziness, and each question is given a score of 0, 2, or 4. A score of 0 means that the condition described in the question never happens, 2 means it sometimes happens, and 4 means it always happens. Followinga study by Whitney *et al.*[14], the DHI scores are graded as mild (0 to 30 points), moderate (31 to 60 points), and severe (61 to 100 points) [15,16].

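### The DHI planning inputs (mean difference 0.41, SD 0.7) do not fit the 0–100 DHI total, and no target difference in DHI points is stated

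*Protocol article*

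**What the plan says.** In the protocol article, the Sample size section says of its basis: "The estimated sample size was calculated considering previous DHI results". The design settings follow: "Calculations are performed using 80% power and a (two-sided) 5% significance level". The result and inputs are: "Estimations indicated 263 individuals for the DHI assessments (effect size = 0.41; standard deviation = 0.7". The same sentence defines the two inputs, "where effect size is the mean difference expected between the two groups and standard deviation is for the population". No unit is attached to either figure. The section then plans 100 participants, 50 per group, with an allowance of 15% for withdrawal.

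The Dizziness Handicap Inventory section describes the instrument: "It consists of 25 questions about daily problems associated with dizziness", and "each question is given a score of 0, 2, or 4". Severity is graded as mild up to 30, then "moderate (31 to 60 points), and severe (61 to 100 points". Nowhere does the article give a target or minimum important difference in DHI points.

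**The concern.** A sample-size calculation tells the reader what difference the trial is built to detect and how reliably. Here the two inputs are tied to the DHI and defined as a raw mean difference and a population SD, yet the SD is far too small for the score the article describes. One of two things must be wrong: the scale or the label. Until that is settled, the reader cannot tell what DHI difference was planned for, cannot check it against the cited studies, and cannot compare the eventual result with the planned effect. The stated number does not help to identify the scale, because the stated inputs do not reproduce it.

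**Working it through.** **Inputs.** From Sample size: difference 0.41, SD 0.7, 80% power, two-sided 5%, 100 enrolled 1:1, 15% withdrawal. From the DHI section: 25 items scored 0, 2 or 4. The formulas are for comparing two independent means with a common SD. That is an assumption, since the article does not name its formula.

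**1. The plan's own figure.** Per group, n = 2(z₀.₉₇₅ + z₀.₈₀)² / (Δ/SD)².
- Δ/SD = 0.41/0.7 = 0.586.
- n = 2 × 7.849 / 0.3431 = 45.8, so 46 per group. The t-test solution is 46.7, so 47.
- Total: 92–94 evaluable. With 15% withdrawal: 92/0.85 = 108.2, so 109; 94/0.85 = 110.6, so 111.

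The stated 263 is not reproduced. It was also not reached with one- or two-sided tests, 80% or 90% power, 0.41 or 0.7 taken as a standardised effect, per-arm or total counts, or inflation for dropout. A total of 263 would correspond to a standardised effect of 0.346, and 263 per arm to 0.244.

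**2. Does an SD of 0.7 fit the DHI total?** Totals are even numbers from 0 to 25 × 4 = 100. The smallest spread for a score with step 2 arises when patients sit on only two adjacent totals, a share p on one and 1 − p on the other:
- SD = 2√(p(1 − p)) = 0.7, so p(1 − p) = 0.1225.
- p = (1 − √(1 − 4 × 0.1225))/2 = (1 − √0.51)/2 = 0.143.
- The other 85.7%, about 86%, share one score.

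This is a floor. Spreading patients over more totals at the same SD needs an even larger share on the commonest one. The same bound applies if 0.7 is the SD of a change, because the difference of two even totals is also even. The inclusion criteria admit unexplained vertigo, unexplained dizziness, Ménière's disease and psychogenic dizziness, with no DHI threshold. Such a population will not put 86% of patients on one total of a 0–100 score.

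**3. Power with the planned sample, keeping the ratio.** Evaluable: 100 × 0.85 = 85, or 42.5 per group.
- Power ≈ Φ(0.586 × √(42.5/2) − 1.96) = Φ(2.70 − 1.96) = Φ(0.74) = 77%. By the t-test with 42 per group it is 76%.
- With all 50 per group it is 83%.

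**4. What the ratio could mean in points.** The article gives no DHI SD in points, so these SDs are assumptions. At 10, 15, 20 and 25 points, 0.586 SD is 5.9, 8.8, 11.7 and 14.6 points. If both figures were means per item (also an assumption), they convert to 0.41 × 25 = 10.25 points and 0.7 × 25 = 17.5 points.

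**The case against.** The best defence is that the article never says points. A mean-per-item or otherwise rescaled score would make 0.41 and 0.7 plausible, the cited studies may explain it, and an article condenses. Moreover, if both figures are on one scale the unit cancels: number and power depend only on 0.586, and converting the same inputs to points changes neither.

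Much of this stands. The sources are not at hand, so the document supports only that it does not state the target in points; it does not show that the trial team has none. Nor is the unit by itself a sizing failure. But the article does more than leave a detail out. It states figures, ties them to the DHI, defines them, and describes a DHI that the SD does not fit. Cancelling units also does not rescue the stated results, since neither 263 nor 80% power after withdrawals follows from the ratio.

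Two stronger inferences should be resisted. First, a reader might argue that 0.41 is impossible because it is smaller than one score step. A difference between group means need not be a multiple of a step; only the SD argument holds. Second, a reader might take 0.41 as a standardised effect. That would need 94–95 per group (2 × 7.849/0.1681 = 93.4, so 94; t-test 95) and would leave about 46–47% power with 85 evaluable. The article's own definition, with a separate SD, contradicts that reading.

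**Conclusion.** The point holds in this form: as written, the DHI planning inputs do not fit the DHI the article describes, and no target difference in DHI points is stated. The evidence is the SD, which would put about 86% of patients on one score. That is implausible for this population rather than a mathematical impossibility.

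On the stated definition, and assuming both figures share some unnamed scale, the shortfall is modest: 46–47 evaluable per group needed against 42.5 expected, and about 76–77% power instead of 80%. The document does not support a conclusion that the trial has under half the patients it needs; that follows only if the source shows 0.41 to be a standardised effect. These figures assume a simple two-group comparison, equal allocation and the full 15% loss. Reconciling 263 with the 100 planned participants, and with the 80 in the Abstract, is a further matter that correcting the unit would not settle.

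**What to change.** In the Sample size section, restate the expected difference and the SD in DHI total points (0–100), or name the scale used and how it converts. Say which cited result each figure comes from and whether the SD is of the score or of the change. Then recompute the number and the power from those values.

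If the ratio 0.586 is kept, replace 263 with 92–94 evaluable and report about 76–77% power for 85 evaluable of 100 enrolled. Only if the source shows that 0.41 is a standardised effect should the definition be corrected, the SD removed and power restated as about 46–47%.

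The cost is checking the cited results and rewording one paragraph. The stated power may become less favourable.

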### Data analysis

Descriptive statistics will be used to describe demographic and baseline characteristics of study participants. Repeated measuresanalysis of variance will be used to test the between-group differences. The accepted level of significance for all analyses will be *P* < 0.05. Data analysis will be conducted by statisticians who are independent of the research team. Analysis will be conducted using SPSS software (SPSS 12.0 KO for Windows ©).

## Discussion

Our study is, to date, the first randomized controlled clinical trial on the efficacy of acupuncture in patients with chronic dizziness.

The word dizziness is used to mean various sensations of body orientation and position that are frequently difficult for patients to describe. Dizziness is difficult to define, impossible to measure, and a challenge to diagnose [22]. Most patients with chronic symptoms are not relieved by medical treatment [23]. Chronic dizziness is a major public health concern. There are millions of patients with chronic dizziness. However, neither the mechanism nor safe and effective treatment methods have been clarified. Any treatment method that reduces chronic dizziness would be an important intervention. Our study will indicate that, despite the difficulty of diagnosis, practitioners can identify patients who can safely benefit from acupuncture. A number of patients with dizziness would prefer acupuncture over pharmacotherapy when our study demonstrates the effectiveness and safety of acupuncture to treat chronic dizziness. This will be especially relevant for patients who do not respond to medical therapy or who experience adverse side effects to drug therapy.

In our study, the acceptability of acupuncture will be reported by patients. Our findings provide insight into a key factor related to effectiveness, namely acceptability of treatment. Acceptability is an important factor because it will impact on the take-up of the treatment offered and the compliance or willingness to see the course of treatment through [24]. We will report on patients’ experiences of acceptability, whether the outcomes from acupuncture are beneficial or not.

However, our study has several limitations. One limitation concerns the fact that we will recruit patients with various types of chronic dizziness, although all the patients referred to acupuncture department will be eligible for the study. However, effectiveness of acupuncture for different types of chronic dizziness is not evaluated. Another limitation is that the therapist is not blinded in the present trial. A blinded study of acupuncture would be challenging to conduct because it is almost impossible to blind acupuncturists to the treatments they are delivering. Therefore, a bias due to unblinding cannot be ruled out.

The results of this study will provide a new evidence-based treatment option for patients suffering chronic dizziness.

## Trial status

The trial is currently in the recruitment phase.

## Abbreviations

DHI: Dizziness handicap inventory; HAD: Hospital anxiety and depression scale; SF-36: Short form-36 quality-of-life questionnaire; VSS: Vertigo symptom scale.
